### Interim analyses {21b}

An interim analysis will take place after 25% of the recruited patients. Furthermore, the DSMB reviews the study progress on a quarterly basis. In order to fulfill this task, the DSMB receives information about protocol deviations, the status of patient recruitment, and the observed cardiovascular AEs and SAEs.

### Methods for additional analyses (e.g., subgroup analyses) {20b}

Interviews and focus groups of the qualitative process evaluation will be analyzed by content analysis [67]. Later on, findings will be cross-mapped with results of the quantitative process evaluation according to the research interests. Methods will be described in more detail in the study protocol for the process evaluation (in preparation).

No prespecified subgroup analyses are planned.

### Methods in analysis to handle protocol non-adherence and any statistical methods to handle missing data {20c}

Participants will be considered adherent to the intervention if they complete the minimal requirements (see Table 3). For participants to be included, they must have baseline values and at least one follow-up value, then the missing data will be imputed using multiple imputation. Details on the type of multiple imputation will be added following a blinded data review.

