### Who will take informed consent? {26a}

Prior to baseline assessment, eligible patients and their relatives will be informed about the study goals, duration of the study, the role of each participant, randomization, and any risks in written and oral forms. After written informed consent from patients, and their relatives by a study physician, baseline assessment (t0) will take place and patients will be randomized (t1). Original patient information and consent forms are available on request from the corresponding author. If a patient does not have any relatives, then persons close to him or her can be consulted. Participation in the study is also possible without relatives or close persons.

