### Prehabilitation

Patients in the intervention group receive a 2-week preventive, intensive, and full-day prehabilitation in selected cardiac-specific rehabilitation facilities (prehabilitation centers) for targeted, holistic preparation for the cardiac procedure. Prehabilitation comprises a multimodal, interdisciplinary therapeutic approach individually adapted to the patients’ needs in order to achieve the best possible physical and mental health status with improved functional reserve prior to the planned cardiac procedure. The prehabilitation program “Karl-Heinz” includes seven modules: (1) sports and exercise therapy, (2) occupational therapy, (3) cognitive training, (4) psychosocial support, (5) disease-specific education, (6) informative talks with relatives, and (7) special hygiene training/nutritional intervention [details see Additional file 3].

To standardize the prehabilitation program, a treatment manual [details see Additional file 3] and a minimum of therapy requirements (see Table 3) was designed in a multidisciplinary team from all participating centers and the two participating health insurance companies (AOK Lower Saxony and AOK Baden-Württemberg). Based on this, a train-the-trainer concept with detailed standard operating procedures (SOPs) and additional training videos was created. All coordinating team members of each prehabilitation center (the so-called “multipliers”) will receive 2 days of train-the-trainer instruction on the individual modules of the treatment manual “Karl-Heinz”. These persons are trained to perform their tasks as “multipliers” a few weeks before the first patient is enrolled.

**Table 3 Tab3:** Overview of the minimum of therapy requirements during prehabilitation program “Karl-Heinz”

**Form of therapy**	**Minimum of requirements**
(1) Sports and exercise therapy	Scope: 1 active unit per day (5 × per week) of 30 min each
	Content: endurance, strength/flexibility, coordination training
(2) Breathing therapy	Scope: 3 times per week of 30 min each
	Content: Group setting with daily self-training
(3) Occupational therapy	Scope: 2 times per week of 30 min each
	Content: see exercise therapy plus tips for the sustainability of prehabilitation
(4) Cognitive training	Scope: 2 times per week of 30 min each
	Content: attention and concentration training
(5) Psychosocial intervention	Scope: 2 times during prehabilitation period

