	Content: Delirium education, preparation for surgery inclusive procedures in the hospital and PMR
(6) Disease-specific education	Scope: 3 units in the prehabilitation period, video training if necessary
	Content: sleep, nutrition, exercise, risk factors, mindfulness, social counseling
(7) Informative talks with relatives	Scope: 1 time during the prehabilitation period
	Content: see treatment manual in the additional file 3

Subsequently, on-site training sessions will be conducted by the multipliers for the intervention staff of the respective prehabilitation centers. The individual elements of the “Karl-Heinz” prehabilitation are not new, but the embedding of a heart-specific program in a structured trans-sectoral concept represents a previously unaddressed need in the care of older patients.

The initial assessment of the individual exercise capacity is carried out by the responsible physicians of the prehabilitation center. Experienced therapists are in regular exchange with the medical staff to individually increase the exercise intensity depending on the primary cardiac disease.

The contents of the individual training interventions are based on current study results, surveys of the participating prehabilitation centers, and interviews with experts. Due to the limited number of studies and the high heterogeneity of existing prehabilitation training intervention studies in cardiological patients, the design of the training forms was based on existing secondary prevention recommendations for cardiological sports and exercise therapy [20–22].

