## Statistical methods

### Statistical methods for primary and secondary outcomes {20a}

Details on statistical analysis are described in a statistical analysis plan (see Additional file 2). The primary endpoint EQ-5D-5L will be evaluated using a joint model for longitudinal data. Stratification factors of age, sex, participation in DMPs, and center will be included as covariates in the model. Time courses of EQ-5D-5L are presented longitudinally for each group, and survival rates are presented descriptively using Kaplan–Meier curves. Treatment effects are reported with 95% confidence intervals. The secondary endpoint HeartQoL is evaluated analogously to the primary endpoint. Secondary endpoints Katz Index, SPPB, MoCa, and HADS are evaluated using mixed linear models, with the factors time point, treatment, and the interaction, and the covariates age, sex, DMP participation, and center. Marginal means are calculated for inter- and intra-group comparisons, and treatment effects are reported with 95% confidence intervals. Likewise, for the analysis of the health economic outcomes, mean differences are calculated in mixed regression models. Because of the skewed distribution of the cost data, the non-parametric bootstrapping procedure, which is also used in the uncertainty analysis of the incremental cost-effectiveness ratio (ICER), is additionally used to calculate the standard errors of the regression parameters. For the analysis of cost-effectiveness, the net-benefit regression procedure is used. Details can be found in the Additional file 1 “Study Protocol”.

Statistical methods in the process evaluation:

For the process evaluation, exploratory sensitivity analyses will be performed to assess the impact of dose, reach, fidelity, and adaption on the intervention’s efficacy. For this purpose, interaction-terms between the treatment variables and these factors will be included in the mixed linear models described above. In addition to the intention-to-treat population, a population will be defined that started the intervention as intended and stays adherent during the follow-up period (starting and adhering estimand).

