Both studies are funded by the “Innovationsauschuss” [Innovation Committee] of the Federal Joint Committee (G-BA). The objective of PRÄP-GO is to evaluate the efficacy of a 3-week prehabilitation program for patients ≥ 70 years of age with frailty or pre-frailty undergoing different kinds of elective surgery. Primary endpoint is the care dependency 1 year after surgery [75]. In comparison, PRECOVERY focusses on patients prior to elective cardiac procedure and the efficacy of a 2-week prehabilitation program for patients ≥ 75 years of age. The co-primary outcomes are QoL and mortality 12 months after the cardiac procedure.

The PRECOVERY study design has several strengths. The multicenter alignment enables the establishment of structures that can be further used in the event of a positive evaluation of the new care form “Karl-Heinz.” Furthermore, the 12-month follow-up has the potential to identify long-term effects of prehabilitation prior to the cardiac procedure (e.g., mortality, QoL or cost-effectiveness). Finally, the study analyzes a broad and representative population in cardiac surgery and cardiology. However, this study has several limitations. Firstly, due to the type of the intervention, blinding of patients and various clinical staff is not possible. In PRECOVERY, only the assessment of outcomes is blinded. Secondly, complete standardization of the intervention is not feasible, as modules are selected according to the individual needs of the patients. To standardize the prehabilitation program “Karl-Heinz,” a treatment manual [see Additional file 3] was created in an expert workshop consisting of physicians, psychologists, sports scientists, and physiotherapists. The manual gives information about the intervention framework and how it can be customized to the individual needs of the participants.

In addition to the treatment manual, the exercise programs are based on current study recommendations in combination with recommendations from secondary prevention of treatment in cardiac patients.

This new form of care that aims in particular to further develop intersectoral care funded by the innovation fund of the Federal Joint Committee (G-BA), the highest decision-making body of the joint self-government of physicians, dentists, hospitals, and health insurance funds in Germany can be considered after positive evaluation to be directly incorporated in the German healthcare system in the long term.

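### As written, the adherence rule fails intervention patients who have nobody to attend the relatives' talk, and the exploratory treatment-by-dose terms reduce to a non-randomised slope within the intervention arm

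*Protocol article*

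**What the plan says.** **Adherence rule.** Section 20c of the protocol article: "Participants will be considered adherent to the intervention if they complete the minimal requirements (see Table 3". Table 3, in the Prehabilitation section, ends with item "7) Informative talks with relatives", and its amount is "Scope: 1 time during the prehabilitation period". No exemption is given. The item above it, disease-specific education, does carry a fallback (video training).

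**Who may enrol.** Section 26a: "If a patient does not have any relatives, then persons close to him or her can be consulted". It adds: "Participation in the study is also possible without relatives or close persons".

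**Tailoring.** The Discussion, under limitations, says that "modules are selected according to the individual needs of the patients".

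**Module list.** The text before Table 3 counts seven modules, the last being "7) special hygiene training/nutritional intervention". Table 3 also has seven items, but one is breathing therapy and none is hygiene or nutrition; nutrition appears only as a topic within item 6.

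**Analyses.** Section 20a plans exploratory sensitivity analyses of how dose, reach, fidelity and adaption affect efficacy: "interaction-terms between the treatment variables and these factors will be included in the mixed linear models described above". In addition to the intention-to-treat population, it defines one that began the intervention as intended and remained adherent through follow-up, called the starting and adhering estimand. Section 6b says controls receive an information folder and standard care. Section 12 describes dose, reach, fidelity and adaption as properties of the intervention.

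**The concern.** There are two separate problems.

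First, Table 3 is the scoring sheet for adherence, and three other statements in the article do not fit it. Some eligible patients cannot meet item 7. Modules are said to vary by need, while the rule asks for every minimum. The adhering population must stay adherent after the procedure, although the only adherence criterion concerns a two-week programme that is over by then. The population therefore cannot be built as described, and part of what it selects on is having someone to bring along.

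Second, a treatment-by-factor interaction asks whether the treatment effect differs across levels of the factor. That needs the factor to vary in both arms. Dose, fidelity and adaption of a programme that controls do not receive cannot do so. A positive coefficient could be reported as dose-response evidence of efficacy when it compares only intervention patients with one another, and those who attended more may have been fitter from the start.

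**Working it through.** **1. The article's own figures.** The sample size section uses a difference of 0.045, SD 0.17, R-squared 0.25, two-sided 5% and 80% power. The adjusted SD is 0.17 × √(1 − 0.25) = 0.147. This gives 169 per arm and 338 in total (power 0.800 by noncentral t). 338 / 0.8 = 422.5, against 422 stated. The figures reproduce and are not in dispute; they supply 422 / 2 = 211 per arm.

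**2. Patients who cannot meet item 7.** The article does not say how many have neither relatives nor close persons, so the share s is assumed. Count = 211 × s; highest attainable adherence = 1 − s.

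| Assumed share | Non-adherent by definition | Highest attainable adherence |
|---|---|---|
| 5% | 11 | 95% |
| 10% | 21 | 90% |
| 20% | 42 | 80% |
| 30% | 63 | 70% |

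If item 7 is read as relatives only, the affected group is larger, because patients whose only contact is a close person join it.

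**3. The adherence window.** Table 3 covers the prehabilitation period, which lies between t1 and t2 in Table 4. Follow-up runs from the procedure to t6, 12 months later. The article states no requirement after the procedure that a patient could meet or miss, so adherence during follow-up has no criterion.

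**4. The interaction.** Let T be arm (0 or 1) and D be dose.

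- Controls coded D = 0: T × D = D for every patient. The design [1, T, D, T × D] has 4 columns and rank 3.
- Controls coded at any other constant c: T × D = D − c + cT, so the interaction is again a combination of the other columns.
- Controls coded missing: they drop out, T is constant, and T × D = D.
- Longitudinal form with five time points and dose-by-time terms: 20 columns, rank 15.
- Main effect of dose omitted, [1, T, T × D]: 3 columns, rank 3 (longitudinal 15 of 15). One slope is estimable, but only the 211 intervention patients inform it.
- A factor that takes values in both arms, for example one measured per recruiting centre: 4 columns, rank 4. If reach were measured that way, its interaction would be identifiable.

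**5. What the estimable slope can pick up.** This is an illustration; all inputs are assumed. Baseline health is standard normal. Sessions = 8 + 1.5 × health + standard normal noise, rounded and held between 0 and 10. The outcome is 0.045 for treatment + 0.05 × health + noise with SD 0.16. The true effect of each session is zero. Over 500 simulated trials the mean slope was +0.025 per session and the coefficient of T was −0.150, although the true treatment effect was +0.045. The slope is entirely confounding. Under other assumptions its size and sign would differ.

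**The case against.** Much of the case on the other side stands.

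- Section 26a lets close persons step in for relatives. That sentence concerns information and consent, but it makes it reasonable to limit certain failure to patients with neither. A reader might infer that every patient without relatives is non-adherent; the article does not support that breadth.
- Section 20a says interaction terms will be included; it does not say that a dose main effect will be. A reader might infer that the analysis cannot be fitted at all. It can, in the reduced form. The fault is then one of meaning: the slope is not a treatment interaction and not a randomised comparison.
- A reader might infer that adherers will be compared with all controls and put a number on the resulting bias. The article names an estimand but gives neither comparator nor estimator, so any such number would rest on an inferred contrast and on assumed inputs.
- Table 3 is a minimum set, so its difference from the module list is weak evidence of error by itself. It matters only because the table is used to score adherence.
- Item 7 refers its content to the treatment manual, and section 20b defers process-evaluation methods to a separate protocol. Neither is shown, and either may settle who may attend or how factors are coded. However, section 20c ties adherence to Table 3 itself, and no further detail can separate an interaction from a main effect when the factor does not vary among controls.

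**Conclusion.** The point holds in limited form. The literal adherence rule contradicts enrolment of patients with neither relatives nor close persons, fits poorly with tailored modules, and is applied over a period in which it has no content. The treatment-by-dose, fidelity and adaption terms are either aliased with the factor's main effect or amount to a within-arm, non-randomised slope; neither shows an effect of these factors on efficacy.

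The consequence is contained. The interaction analyses are labelled exploratory, intention-to-treat is kept, and the interactions enter the mixed models used for Katz Index, SPPB, MoCa and HADS, not the joint model for EQ-5D-5L. It would be too strong to say that the adherence analyses are void or bound to favour the intervention: the number misclassified (11 to 63 under assumed shares of 5% to 30%) and the size and direction of any bias depend on quantities the article does not give. The rank result rests on one condition only, that controls have no prehabilitation dose, fidelity or adaption that varies.

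**What to change.** Before unblinding:

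1. Score adherence only on Table 3 items that apply to the patient, leaving item 7 out when no relative or close person is available, and state who may attend that talk.
2. Assess adherence over the prehabilitation period only, and reword the starting and adhering population to match.
3. Reconcile Table 3 with section 26a, the module list and the Discussion's statement on tailoring. Which therapy content is right is for the clinical team.
4. Report dose, fidelity and adaption as associations within the intervention arm, adjusted for baseline prognostic variables, and not as treatment interactions. This keeps the process-evaluation questions.
5. For the effect of adhering, add a complier-average (instrumental-variable) analysis with randomised arm as instrument, adherence as exposure and all randomised patients included.

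The cost is analysis-plan wording and one modest extra analysis. The complier analysis needs an exclusion restriction: allocation must affect the outcome only through adherence as defined. Patients who complete part of the programme and benefit would breach it, so the assumption should be stated. Its intervals are also wider. With no control access and an assumed 70% adherence, the estimate is the intention-to-treat effect divided by 0.7, so estimate and interval width grow by about 1 / 0.7 = 1.43. For the same reason item 1 should come first: patients counted as non-adherent only because of item 7 would inflate the complier estimate.

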### Outcomes {12}

The co-primary outcomes are the QoL and mortality after 12 months. The QoL is measured by the EuroQol questionnaire (EQ-5D-5L, [23]). The EQ-5D-5L consists of five dimensions (mobility, self-care, usual activities, pain/discomfort, and anxiety/depression) and is an instrument for measuring QoL and determining quality-adjusted life years in health economic studies [23, 24]. Each dimension is scored on a 5-point scale. The responses to the individual items are combined into a QoL index using established algorithms. In addition, patients rate their health status on a visual analog scale (EQ-VAS; range 0–100) [23].

The following secondary outcomes measures are defined:Activities of daily living (ADL) measured by Katz Index [25, 26]Physical performance rated by Short Physical Performance Battery (SPPB; [27])Cognitive performance measured by Montreal Cognitive Assessment Test (MoCa; [28, 29])Disease-specific QoL assessed by Heart Quality of Life Questionnaire (HeartQoL; [30])Anxiety and depression detected by Hospital Anxiety and Depression Scale (HADS; [31–33])Healthcare costs after 12 months. Healthcare resource utilization within 12 months after the cardiac procedure. During follow-up, all direct medical and non-medical healthcare-related resource utilization will be monitored using a validated questionnaire for health-related resource use by older patients (Fragebogen zur Inanspruchnahme medizinischer und nicht-medizinischer Versorgungsleistungen im Alter (FIMA; [34]) in combination with routine data transmitted by the AOK Lower Saxony and AOK Baden-Württemberg.

Further endpoints are as follows:

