### Sample size {14}

A total number of 422 patients is planned for this intervention trial. The number of cases was planned on a confirmatory basis in order to be able to answer the primary questions with a power of 80%. A total of 338 patients (169 per treatment group) is sufficient to show a clinically relevant difference of 0.045 points in EQ-5D-5L at t6 with 80% power at the generally accepted two-sided significance level of 5%. It is assumed that the common standard deviation of the EQ-5D-5L is 0.17 and that the observations on the covariates have an R-squared of 0.25. Since this is a longitudinal study, a dropout rate of up to 20% is assumed, so a total of 422 patients will be recruited. The case number calculation was performed in nQuery version 8. The definition of a clinically relevant difference of 0.045 was based on the publication of McClure et al. [62], who restricted a minimal clinically relevant difference to values between 0.037 and 0.069 [62]. Since the publication did not include results on the German population, a value was chosen that was approximately 10% lower than the average of the countries considered in the publication. The assumption of a standard deviation of 0.17 is based on observations by [63], who observed a standard deviation of 0.171 at baseline and a standard deviation of 0.170 at 12-month follow-up in a sample of 1927 diabetes-2 patients [63].

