### Recruitment {15}

The recruitment measures in PRECOVERY are integrated into the standard procedures of the participating recruiting centers. In these centers, patients scheduled for cardiac procedures in 4–6 weeks will be screened, informed, recruited (t0), and randomized (t1) according to the inclusion and exclusion criteria during a preoperative appointment in cardiology or cardiac surgery departments. To support the recruitment process, all referring centers will be informed about the study in advance and additional flyers will be produced to increase patient interest.

If the recruitment is not running well, the evaluation concept is designed through the use of the FIMA questionnaire in such a way that an extension to the inclusion of insured persons from other health insurance funds is also conceivable in Lower Saxony on the basis of the legal basis §630a German civil code.

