## Assignment of interventions: allocation

### Sequence generation {16a}

After baseline assessment, randomization will be 1:1 stratified by study center, patient age (< 81 years vs. ≥ 81 years), and gender (block randomization with random block lengths). Randomization will be performed by unblinded study physicians at the recruiting centers. After randomization, the patient will be informed about the respective allocation. In case of allocation into the intervention group, the prehabilitation center will be contacted by the unblinded study physician. The individual outcome assessors at the recruiting centers remain blinded.

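### The analysis set requires at least one follow-up value, so inclusion depends on a post-randomisation event, and the rule is limited neither to quality of life nor to values missing while alive

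*Protocol article*

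**What the plan says.** All references are to the protocol article.

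- **Inclusion and imputation.** On non-adherence and missing data, {20c} requires of participants that "they must have baseline values and at least one follow-up value, then the missing data will be imputed using multiple imputation". It then adds: "Details on the type of multiple imputation will be added following a blinded data review". Only the type of imputation is deferred; the entry condition is already stated. The section names no endpoint, does not mention death and does not say which visit supplies the follow-up value.
- **Population.** The process-evaluation paragraph of {20a} says: "In addition to the intention-to-treat population, a population will be defined that started the intervention as intended". It therefore takes an intention-to-treat population as given.
- **Endpoints.** Section {12} states: "The co-primary outcomes are the QoL and mortality after 12 months".
- **Model.** Section {20a} states: "The primary endpoint EQ-5D-5L will be evaluated using a joint model for longitudinal data". Survival is shown descriptively with Kaplan–Meier curves.
- **Knowledge of allocation.** Section {16a} states: "After randomization, the patient will be informed about the respective allocation". Under {17a}, only outcome assessors are blinded.
- **Visits.** In Table 4 ({13}), EQ-5D-5L is collected at t1 and then from t2, before the procedure, through t6. Section {15} places the procedure 4 to 6 weeks after recruitment.

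**The concern.** Randomisation protects a comparison only while the arms are kept as randomised. A condition that can be met or failed only after allocation gives up that protection. Here there is a plausible route to unequal exclusion: patients are told their arm, and the whole prehabilitation stay falls between t1 and t2. A control may leave on learning the allocation, and an intervention patient may have an event or withdraw during the stay. Either could leave no follow-up value and so drop out of the analysis.

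Mortality makes this sharper. Vital status needs no questionnaire, and {18a} says deaths at 30 days and one year are recorded systematically. If the same rule governs that endpoint, a known death can be excluded because no follow-up score preceded it.

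The second half of the rule raises a related issue. In patients aged 75 or older some t6 scores will be absent because the patient has died. Such a value does not exist, whereas a questionnaire not returned by a living patient is missing. The rule treats absent data as one category.

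**Working it through.** **1. The plan's own figure.** Inputs from {14}: difference 0.045, SD 0.17, covariate R-squared 0.25, two-sided 5%, power 80%, dropout up to 20%.

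- Residual SD = 0.17 × √(1 − 0.25) = 0.1472.
- n per arm = 2 × (1.960 + 0.842)² × 0.1472² / 0.045² ≈ 168.0, which rounds up to 169, or 338 in total. A t-based calculation gives power 0.800 at 169 per arm.
- 338 / 0.80 = 422.5, stated as 422.

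The sample size reproduces. This point disputes no stated number.

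**2. Who the rule removes.** This depends on which visit counts as follow-up, and the article uses the term in more than one sense.

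- If t2 counts, as the description of time points after the intervention in {21a} would allow, only patients who leave before t2 are lost.
- If only visits after the procedure count, as the wording on one-year follow-up in {6a} and {30} suggests, patients who complete t2 but die around the procedure are lost too.

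Neither set is all randomised patients.

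**3. Size of the shift in the EQ-5D-5L difference.** The exclusion rates and the gap are assumptions, because the article gives none.

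Let a share e of an arm be excluded, with mean g below the retained mean m. The full-arm mean is m − e × g, so the retained mean is too high by e × g. The between-arm difference is therefore off by |e₁ − e₂| × g.

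| Excluded, one arm v the other | g | Shift | Share of 0.045 |
|---|---|---|---|
| 2% v 5% | 0.1 | 0.03 × 0.1 = 0.003 | 7% |
| 2% v 5% | 0.2 | 0.03 × 0.2 = 0.006 | 13% |
| 5% v 10% | 0.1 | 0.05 × 0.1 = 0.005 | 11% |
| 5% v 10% | 0.2 | 0.05 × 0.2 = 0.010 | 22% |

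The sign depends on the arm that loses more patients. More exclusions among controls understate a benefit; more in the intervention arm overstate it. With equal exclusion and an equal gap the shift is zero. At 2% to 10% overall, the rule would remove 422 × 0.02 ≈ 8 to 422 × 0.10 ≈ 42 randomised patients.

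**4. Deaths lost if the rule governs mortality.** Assume 5% to 15% one-year mortality, with 10% to 30% of deaths before the first follow-up value. Then 422 × 0.05 × 0.10 ≈ 2 to 422 × 0.15 × 0.30 ≈ 19 deaths would go uncounted.

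**5. Imputation beside the joint model.** A joint model usually links the longitudinal score to an event time, so death ends the series as an event, and incomplete series enter without prior imputation. Section {20c} imputes missing data generally, with no exception for death. The two can coexist if imputation stops at death, but the article does not say so.

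**The case against.** The strongest reply is that the SAP, which is not shown, will settle the analysis sets and the handling of death, and that {20c} itself defers imputation detail. This stands for the imputation model, whose absence is no finding. It does not cover the entry condition, which the article states outright.

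Several other objections hold in part:

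- **Intention-to-treat.** The phrase stands in the process-evaluation paragraph and does not define the set for the co-primary analyses. The conflict is therefore an inconsistency between two sections, not a direct contradiction of a formal definition.
- **Mortality.** The sentence is about missing values, and a recorded death could be taken as the follow-up value for mortality. Removal of early deaths is thus the literal reading, not a declared intention. The text does not exclude it.
- **Early deaths.** If t2 counts as follow-up, most peri-procedural and later deaths stay in, and only exits during the short wait are affected.

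A reader might go further and infer that the plan will assign quality-of-life scores to patients who have died. The article does not say so. It is silent on death, and its choice of a joint model makes that intention less likely. One might also size the problem by comparing survivor-like values with a score of 0 at death. Neither the plan nor the fix below scores death as 0, so that contrast does not measure the gap between them. Nor does imputation by itself overstate the information at t6, since properly combined multiple imputation carries its uncertainty into the standard errors.

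**Conclusion.** The point holds in a bounded form. The follow-up requirement makes the analysis set depend on a post-randomisation event in a trial whose patients know their arm. It does not fit the intention-to-treat population mentioned elsewhere, and as worded it reaches the co-primary mortality endpoint. Separately, {20c} does not distinguish values missing while alive from values that do not exist after death, and it is not reconciled with the joint model.

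On the assumed differential exclusion above, the shift in the EQ-5D-5L difference is 0.003 to 0.010, or 7% to 22% of the target for which the sample size is said to be "sufficient to show a clinically relevant difference of 0.045 points in EQ-5D-5L at t6 with 80% power". That is modest but avoidable, and it could run in either direction. The loss of about 2 to 19 deaths is conditional on the literal reading for mortality and on the assumed rates. None of these rates comes from the article, so the figures illustrate the scale and do not estimate the actual bias. The planned 338 and 422 are unaffected.

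**What to change.** Amend {20c}, and align {20a} and the SAP with it:

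- Delete the requirement for a follow-up value.
- Analyse all randomised patients in their allocated arm for both co-primary endpoints.
- Use vital status for every randomised patient in the mortality comparison, whether or not any questionnaire was completed.
- Keep patients with baseline data only in the longitudinal likelihood.
- State that death is the event in the joint model and that scores after death are not imputed.
- Limit any multiple imputation to values missing while the patient was alive.

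The cost is revised wording and a little more programming. No new data are needed and the sample size does not change.
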